
### Participant timeline {13}

The participant timeline is presented in the SPIRIT figure: schedule of enrollment, interventions, and assessments (Fig. 2).

**Fig. 2 Fig2:**
[figure not shown]
SPIRIT figure: Schedule of enrollment, interventions, and assessments. Asterisk symbol (*) indicates the following: if indicated in case of intraoperative complications. DOS, day of surgery; POD, postoperative day; LRYGB, laparoscopic Roux-en-Y gastric bypass; SURG-TLX, surgery task load index

### Sample size {14}

The sample size was calculated for the primary outcome (operating time). As the study is mainly based on knowledge from preclinical studies and there is not much guiding literature in the clinic, some assumptions had to be made at the beginning. We assume that an operator needs approximately 75 min to perform a gastric bypass using 3D HD imaging, while performing the exact same operation using 2D 4K imaging takes 90 min. This assumption is supported by the literature, which states that a gastric bypass operation takes approximately 90 min for experienced operators using 2D laparoscopy, by the results of studies that showed a time savings of approximately 15 min using 3D laparoscopy, and by the results of our preliminary study, which showed an average time savings of almost one fifth using 3D laparoscopy compared to 2D 4K [18–20]. The EAES systematic review also suggests an average difference of 15 min for procedures involving laparoscopic suturing [2]. Calculation is as follows: sequential analysis with a maximum of 2 looks (group sequential design, O’Brian-Fleming alpha spending), overall significance level 2.5% (one-sided); the sample size was calculated for a two-sample *t*-test, minimal detectable difference = 15, standard deviation = 15, power 90%; futility bound of 0 at interim analysis; number of subjects at interim 22.3, final: 44.6. Sample size calculation is based on RPACT (R package version 3.2.1) [21].

Therefore, we will recruit 48 patients in blocks of four with gastric bypass indications and randomize them to the two groups (2D 4K and 3D HD).

### Recruitment {15}

The surgeon recruits patients for the study. These are patients who have already decided to undergo gastric bypass surgery independently of the study and who meet all of the indications for the procedure. Recruitment for the study is therefore dependent on the general performance of gastric bypass surgery at Clarunis and will continue until the defined sample size is reached. Given that Clarunis is a certified reference center for bariatric surgery and that gastric bypass is the most common type of bariatric surgery, we expect the study to take approximately 2 years to complete.

## Assignment of interventions: allocation

### Sequence generation {16a}

Patients are randomly assigned to the four possible sequences using block randomization with a block size of four patients. The two groups will be assigned according to the randomization list, and surgery will be performed based on these groups using either 2D 4K or 3D HD imaging. If a patient fails to complete the study, the next patients will follow the list at the same point as the failed patient. There is no prior stratification.

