### Trial design {8}

This study is designed as a single-center, parallel-group, superiority, randomized, controlled, prospective trial. All patients will have gastric bypass surgery and will be operated with 3D HD or 2D 4K imaging depending on the intervention group assignment. The patient allocation is 1:1.

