### Concealment mechanism {16b}

This is not applicable as the study is single-blind. It is only the patient who is not informed of the imaging technique used; the surgeon is informed.

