### Implementation {16c}

Patients are randomized 1 day before surgery using a computer-generated allocation list (generated using R version 4.1.3). The randomization list is linked to the study’s data management program (REDCap) by the project statistician. The operating surgeon recruits the patients and collects the data needed to conduct the study. The day before surgery, the surgeon enters the data into the electronic case report form (eCRF) in REDCap, which is designed for this study. Once the patient is enrolled in the study and the required data is entered into the system, the patient is automatically assigned to an intervention group using the linked randomization list. This ensures that surgeons have no influence on patient allocation. However, they are unblinded and are informed on the preoperative day which laparoscopic system will be used for the next surgery in the study. This is unavoidable, which is why our study is single-blind. Only the patients are blinded.

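### The fixed, published block of four lets unblinded recruiting surgeons deduce about one third of allocations in advance, and the protocol miscounts its sequences and treats concealment as blinding

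*Protocol article*

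**What the plan says.** The relevant statements in the protocol article are these.

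- Trial design {8}: "The patient allocation is 1:1".
- Sample size {14}: "Therefore, we will recruit 48 patients in blocks of four with gastric bypass indications and randomize them to the two groups".
- Sequence generation {16a}: "Patients are randomly assigned to the four possible sequences using block randomization with a block size of four patients". The section adds "There is no prior stratification" and a replacement rule: "If a patient fails to complete the study, the next patients will follow the list at the same point as the failed patient".
- Concealment mechanism {16b}: "This is not applicable as the study is single-blind".
- Implementation {16c}: "The operating surgeon recruits the patients and collects the data needed to conduct the study". The statistician links a computer-generated list to REDCap. The surgeon enters the data on the day before surgery, and the system then shows the arm. The protocol concludes: "This ensures that surgeons have no influence on patient allocation". The same section says that surgeons are unblinded and learn each allocation before operating.

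Study setting {9} names three operating surgeons at one centre. Role of sponsor {5c} says that the sponsor-investigator is one of them.

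**The concern.** There are two errors of statement and one weakness of design.

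First, the number of sequences is wrong for the stated block size and ratio. Either the sentence is a slip, or the list leaves out two valid sequences. The second case would make allocation more predictable.

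Second, concealment means that the person entering a patient cannot know that patient's arm beforehand. Blinding concerns what is known after assignment. Concealment applies to every randomised trial and matters most where the operator cannot be blinded. Declaring it inapplicable also contradicts the procedure that the protocol sets out in the next section.

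Third, a small block of one fixed size on one shared list lets a surgeon who knows the earlier allocations work out some later ones. The same surgeons recruit, enter the data that release the arm, and work under a stated hypothesis that favours 3D HD. At stake is selection bias in operating time, the primary outcome. Outcomes {12} itself lists BMI as a confounder and previous abdominal surgery as a possible complicating factor. The primary test is an unadjusted t-test.

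**Working it through.** **Inputs.** Block size 4 and no stratification ({16a}); 1:1 allocation ({8}); 48 patients, hence 48/4 = 12 blocks, and SD 15 min ({14}); one-sided 2.5% level ({20a}).

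**Number of sequences.** C(4,2) = 4!/(2!·2!) = 6: AABB, ABAB, ABBA, BAAB, BABA, BBAA. The stated figure of four does not reproduce.

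**Allocations known with certainty.** An allocation is certain once one arm has used both its places in the block. AABB and BBAA have two such positions; the other four sequences have one each.

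- Share: (2 + 2 + 1 + 1 + 1 + 1)/(6 × 4) = 8/24 = 1/3.
- Expected number: 48/3 = 16. The possible range is 12 (one per block) to 24 (two per block).

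**Best guess.** The guess is always the arm that is behind in the block. The chance of being right is 1/2 at position 1 and 2/3 at position 2. At position 3 it is (2/3)(1/2) + (1/3)(1) = 2/3, and at position 4 it is 1. The mean is (1/2 + 2/3 + 2/3 + 1)/4 = 17/24 = 70.8%, against 50% without knowledge of the block.

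**If only four sequences are on the list.** All 15 ways of choosing four from six were enumerated. The certain share is 7/16 (43.75%) or 1/2, that is 21 to 24 of 48, and the best guess is right 75% or 81% of the time.

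**Effect of block size, when the block is fixed and known** (certain share = 1/(m+1), with m patients per arm per block):

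| Block | Certain |
|---|---|
| 4 | 33% |
| 6 | 25% |
| 8 | 20% |
| 24 | 7.7% |

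For a block of 24 the best guess is right 61% of the time.

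**Illustration of consequence, under assumption.** Suppose a guess shifts the entered patient's expected operating time by δ: minus δ when 3D HD is expected, plus δ when 2D 4K is expected. All three surgeons act the same way and there is no true effect. The values δ = 3 and 5 min are assumptions; the protocol gives no figure.

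- *Acting at every non-tied position.* Right minus wrong guesses per block: position 2 gives 2/3 − 1/3 = 1/3; position 3 gives 1/3 (non-tied one time in three, then always right); position 4 gives 1. The total is 5/3. Over 12 blocks that is 20 net, or 10 per arm. The bias is 2 × δ × 10/24 = 0.833δ, which is 2.5 min for δ = 3 and 4.2 min for δ = 5.
- *Acting only at certain positions.* 16 patients, 8 per arm: the bias is 2 × δ × 8/24 = 0.667δ, which is 2.0 and 3.3 min.

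The standard error of the difference with 24 per arm is 15 × √(2/24) = 4.33 min. Simulation (200,000 trials, six sequences, t-test) gives these one-sided type I errors:

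| Behaviour | δ = 3 | δ = 5 |
|---|---|---|
| Every non-tied position | 8.0% | 14.5% |
| Certain positions only | 6.6% | 11.0% |

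Using the two planned looks with critical p-values 0.0015 and 0.0245 changes these by about 0.1 percentage point at most.

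**Replacement rule.** Where a failed patient's arm had already been revealed, the replacement takes the same list position and its arm is known in advance. This is not counted above.

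**The case against.** Concealment of the list does exist. Under Implementation {16c} the list sits in REDCap and the arm appears only after enrolment and data entry. A reader might infer from {16b} that the list is open to the surgeons; the protocol does not support that. This part of the objection stands, and what remains is a wrong statement plus predictability of the block.

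Steering is possible but not shown. By Recruitment {15}, patients have already chosen surgery independently of the study, and they are randomised one day before it. Entry order therefore largely follows the operating schedule. Exploiting a deduced allocation would mean reordering that schedule, or delaying or not entering a patient. Nothing says that anyone tracks the blocks. Against this, {11c} leaves planning to the operating surgeon, who also recruits, so the route is narrow rather than closed.

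A reader might also infer that up to half of all allocations are predictable. That needs the list really to omit two sequences, and the only support is one sentence that may be a slip. The supportable figure is one third.

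The error rates depend on behaviour. A shift of plus or minus 3 (5) min is a 6 (10) min swing, applied by every surgeon in one direction. If the guessing strategy is used only half the time, the error is about 4.4% (6.6%).

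Finally, {20a} plans exploratory adjustment for age, sex, BMI and possibly other parameters. This may absorb some bias from measured covariates, but it does not protect the primary test.

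**Conclusion.** The point holds in a limited form. The sequence count is wrong (six, not four), and {16b} mistakes concealment for blinding and conflicts with {16c}. With all six sequences in use, one third of allocations (16 of 48 expected) can be deduced beforehand and 71% guessed. This assumes that the surgeons know the block size, which is published, and follow earlier allocations on their shared list. The assurance that surgeons have no influence covers the list, but not who is entered next.

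It would go too far to conclude that the trial is biased or that its type I error is 8% or 14%. Those figures show only what consistent steering of an assumed size would do. The stated sample size and alpha allocation are not affected.

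**What to change.** 1. In {16a}, correct the number of sequences to six. The statistician should confirm that all six can occur on the list in use.
2. In {16b}, replace the declaration with the mechanism already in {16c}: the list is held in REDCap and the arm is released only after enrolment and data entry. Limit the assurance in {16c} to the list.
3. Recruitment began in August 2023 (Trial status), so for the unused part of the list the statistician should generate larger or randomly varying blocks, not disclosed to anyone who recruits. Keep 12 per arm at the interim and 24 at the end where this is still possible. Two blocks of 24 (12 + 12) would meet both counts and cut certain allocations to 7.7%, but they fit only if the list is wholly unused.
4. If no unused list remains, correct the text and report the predictability among the limitations. The Limitations section does not mention it.

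The cost is a regenerated list, a minor amendment, and slightly less balance between arms over calendar time.

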### Criteria for discontinuing or modifying allocated interventions {11b}

Gastric bypass surgery and its pre- and post-operative procedures are performed as standard. The study only influences the choice of laparoscopic imaging used during surgery. Consequently, the criteria for stopping or modifying the allocated procedures for a given subject will depend on the responsible operator in consultation with their multidisciplinary obesity team and within the given national guidelines of the SMOB. If the indication is no longer given due to changed inclusion or exclusion criteria, the intervention will not be performed. In addition, patients may withdraw from the study at any time for any reason without consequence.

Patients excluded prior to gastric bypass surgery will be replaced to maintain the required number of procedures for comparison. Patients who are excluded after surgery because they do not return for their first post-operative visit at 3 months, and therefore no post-operative follow-up can be documented, will not be replaced, as this follow-up is only one of the secondary endpoints of the study.

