### Methods in analysis to handle protocol non-adherence and any statistical methods to handle missing data {20c}

To ensure data quality, the monitoring plan checks the data for missing data, extreme outliers, and erroneous entries prior to statistical analysis. Missing data will be closely monitored. However, missing data due to noncompliance or dropout should remain within the expected minimum. Dropouts related to the primary outcome will be replaced to achieve the required number of participants and thus significant results. There is no need to replace dropouts for the secondary outcomes, and there are no plans to use multiple imputation.

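### Reusing a failed patient's list position tells the recruiting surgeon the replacement's arm in advance

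*Protocol article*

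**What the plan says.** Sequence generation {16a} specifies "block randomization with a block size of four patients", adds "There is no prior stratification", and sets the replacement rule: "If a patient fails to complete the study, the next patients will follow the list at the same point as the failed patient". Trial design {8} states "The patient allocation is 1:1".

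On timing, Implementation {16c} says "Patients are randomized 1 day before surgery using a computer-generated allocation list", and of the surgeons that "they are unblinded and are informed on the preoperative day which laparoscopic system will be used for the next surgery". The same section has the operating surgeon recruit patients and enter the data that trigger allocation. It concludes that surgeons cannot influence which arm a patient gets.

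Two other sections say who is replaced:
- Section {11b}: "Patients excluded prior to gastric bypass surgery will be replaced to maintain the required number of procedures for comparison". It adds that patients lost after surgery, at the 3-month visit, are not replaced.
- Section {20c}: "Dropouts related to the primary outcome will be replaced to achieve the required number of participants and thus significant results". It sees no need to replace dropouts for the secondary outcomes.

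**The concern.** A patient receives a list position only at randomisation, so anyone excluded between then and surgery leaves behind a slot whose arm the surgeons already know. The next recruit fills that slot. The recruiter then knows the arm before approaching, consenting or entering the patient, and could let expected difficulty influence who goes next. Blinding the patient does not protect against this, because the surgeon makes the choice.

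At stake is the comparability of the arms on operating time, the primary outcome, in a one-sided test whose hypothesis favours 3D. No analysis can fully undo selection at entry.

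The rule in {16a} is also worded more widely than {11b} and {20c}. It covers anyone who does not finish the study, whereas the other two sections confine replacement to patients without a primary outcome.

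**Working it through.** **The plan's own figures.** Inputs from Sample size {14}: difference 15 min, SD 15 min, one-sided 2.5%, power 90%, two looks with O'Brien-Fleming-type spending, futility bound 0. The fixed-design t-test needs a total of 44.04. The group sequential inflation factor is 1.0116, and 44.04 × 1.0116 = 44.55, with half of that, 22.28, at interim. The protocol states 44.6 and 22.3. The critical p-values come out at 0.00153 and 0.02450, against 0.0015 and 0.0245 stated. The sample size is not at fault.

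**How predictable an allocation is.** A balanced 1:1 block of four has six orders. If all six are equally likely and earlier allocations are known, the best guess is right with probability 1/2, 2/3, 2/3 and 1 at positions 1 to 4.
- First use of a slot: mean (0.50 + 0.67 + 0.67 + 1.00)/4 = 71%. The arm is certain for (0 + 0 + 1/3 + 1)/4 = 33% of slots.
- Reused slot: certain at every position, 100%.

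**Possible size.** The protocol gives no dropout rate and no figure for how well operating time can be foreseen, so this is an illustration. Assumptions: no true effect, SD 15, 24 per arm, a share v = 0.2 to 0.4 of the variance predictable at baseline, one final t-test at 2.5%, and the k hardest-predicted patients excluded in the 3D arm only.

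The expected bias when an average patient replaces each one is (k/24) × 15√v × m. Here m is the mean standard normal score of the top k of 24, about 1.73 for k = 2 and 1.43 for k = 4.
- k = 2: 0.0833 × 6.71 × 1.73 = 1.0 min (v = 0.2); 0.0833 × 9.49 × 1.73 = 1.4 min (v = 0.4).
- k = 4: 0.1667 × 6.71 × 1.43 = 1.6 min; 0.1667 × 9.49 × 1.43 = 2.3 min.

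If the surgeon instead takes the easier of two candidates for each known slot, the mean score of the replacement falls by 1/√π = 0.56. That adds (k/24) × 15√v × 0.56, which is 0.3 to 0.4 min for k = 2 and 0.6 to 0.9 min for k = 4.

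Simulated one-sided type I error (40,000 null trials per setting; the lower figure is v = 0.2, the upper v = 0.4):

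| What happens after the exclusions | k = 2 | k = 4 |
|---|---|---|
| Slot reused, average patient | 4.1–5.1% | 5.7–7.9% |
| Next unused allocation | 4.2–5.3% | 6.0–8.9% |
| No replacement | 4.4–5.5% | 6.5–9.4% |
| Slot reused, easier of two candidates | about 5–6% | about 8–11% |

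Without exclusions the rate is 2.5%. The first three rows are nearly equal, so the rise in them is due to selective exclusion and not to slot reuse. Only the step from the first row to the last depends on knowing the arm of the reused slot: roughly 1 percentage point for k = 2 and 2 to 3 for k = 4.

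**The three replacement statements.** Read literally, {16a} would replace a patient whose operating time is already recorded. Section {11b} rules that out for patients lost after surgery, and {20c} limits replacement to the primary outcome. These two are more specific and agree with each other, so the wording in {16a} is too wide.

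**The case against.** The opportunity is narrow. The window runs from the day before surgery to the operation. Section {11b} ties cancellation to a lost indication or the patient's own withdrawal, and has the operator act in consultation with the obesity team. Patients are blinded, so their withdrawal should not depend on arm. First-time allocations are released by REDCap only after enrolment and data entry, and fixed blocks of four already make a third of slots deducible. All of this stands, and it limits how many slots could be reused.

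The simulated exclusions are also severe, since a surgeon sees patients one at a time and cannot rank a whole arm. If instead the first k patients from the hardest quarter are dropped, with a correlation of 0.3 to 0.7 between foreseen difficulty and operating time, type I error is 3.2–4.8% (k = 2) and 4.2–7.7% (k = 4) with average replacements. The direction is the same and the size somewhat smaller.

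A reader might infer three stronger things that the documents do not support:
- That slot reuse itself causes the rise to 4–8%. The table shows otherwise.
- That the sample size is not fixed, because operated patients could be replaced. Sections {11b} and {20c} exclude this.
- That concealment and analysis as randomised fail for the whole trial. Only reused slots are newly exposed.

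The reference to significance in {20c} is poor wording, but it has no operational effect of its own and does not show intent.

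**Conclusion.** The concern holds in limited form. For a reused slot the recruiting surgeon knows the replacement's arm with certainty, so the assurance in Implementation {16c} fails there. How often this would occur is unknown, and nothing shows that it would be exploited.

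Under the stated assumptions, excluding 2 (4) hard 3D cases takes one-sided type I error from 2.5% to about 4–5% (6–8%) whatever the replacement rule. Picking the easier of two candidates for the known slot takes it to about 5–6% (8–11%). Only that last step is attributable to slot reuse. The rule should be changed because the change is cheap and reuse offers nothing beyond exact arm balance, but it does not invalidate the design.

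**What to change.** - **Sequence generation {16a}:** delete slot reuse. Each randomised patient keeps the number and allocation, and any additional patient takes the next unused allocation until 48 have been operated.
- **Analysis:** analyse every operated patient in the randomised arm, including any operated with the other imaging system.
- **Reporting:** list all exclusions between randomisation and surgery by arm, with reasons. This exposes selective exclusion but does not prevent it.
- **Wording:** restrict the condition in {16a} to patients without an operating time, so that it agrees with {11b} and {20c}. In "Dropouts related to the primary outcome will be replaced to achieve the required number of participants and thus significant results" delete the last four words.

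The cost is protocol wording, a REDCap list setting, a few extra list entries and slightly unequal arms. The loss from imbalance is small: 26 against 22 carries the information of 2 × 26 × 22/48 = 23.8 per arm instead of 24. The next unused slot in a block of four can still be guessed 71% of the time on average, so the change reduces predictability without removing it.
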